#### **MRI Time Points**

Two MRIs will be performed for each participant at the following points:

- MRI1: (baseline) prior to the start of neoadjuvant treatment. Any additional lesions identified on MRI will be addressed per standard of patient care. If patient cannot have MRI, contrast enhanced digital mammography(CEDM) is allowed in place of MRI.

- MRI2 (optional but highly recommended): (*post Gammapod, MR Linac, or Cyberknife*) After MRI1, before surgical excision. The purpose of this optional scan is to test response to radiotherapy.

#### MRI post processing

Subtraction series of all dynamic post contrast sequences will be obtained. Maximum Intensity Projection (MIP), and ADC maps of the Diffusion weighted series will be obtained. DWI difference will be computed between baseline and post radiation therapy.

### **5.1.15 Patient and Physician Cosmesis Forms (Appendix III and IV)**

Both patients and physicians will fill out patient cosmesis forms at baseline and per Section 5.4 time and events table.

### **5.1.16 Oncotype Testing**

It is recommended that Oncotype or mammaprint testing be performed or considered on the biopsy specimen as the response of the tumor to radiation may alter Oncotype or Mammaprint testing results.

## **5.2 Procedures During Treatment**

### **5.2.1 Baseline/Prior to Radiation Therapy**

- Breast Assessment/Examination
- Breast Imaging (see section 5.1.10 for details)
- Breast MRI or contrast enhanced digital mammography(CEDM) (see section 5.1.14 for details)
- History and Physical Exam (including Performance Status)
- Baseline adverse event assessment
- Baseline breast digital pictures
- Patient and Physician Cosmesis Forms
- Optional blood samples for correlative studies within 30 days prior to radiation
- Tumor sample from diagnostic biopsy
- Optional Tumor Sample within 30 days prior to radiation.
- Pregnancy Test (if applicable)

### **5.2.2 Within 14 days (+2 days) after Radiation**

- Optional tumor sample

### **5.2.2. 1 month after Radiation**

- History and Physical Exam
- Breast Assessment/Examination
- Toxicity/Adverse event evaluation
- Optional Blood Samples
- Optional Breast MRI (at least 4 weeks after XRT and before surgery)

### **5.2.3 Surgical Procedure**

Tumor Sample for Research at time of surgery

### **5.2.4 1 month after Surgery**

Optional Blood Samples

**5.2.5 3 months after Radiation**

Toxicity/Adverse event evaluation (via phone call by study team member)

**5.2.6 6 Months after Radiation**

- History and Physical Exam
- Breast Assessment/Examination
- Toxicity/Adverse event evaluation

**5.2.7 12 months after Radiation**

- History and Physical Exam
- Breast Assessment/Examination
- Toxicity/Adverse event evaluation
- Breast Imaging

**5.2.8 24 months after Radiation**

- History and Physical Exam
- Breast Assessment/Examination
- Toxicity/Adverse event evaluation
- Breast Imaging

**5.2.9 36 months after Radiation**

- History and Physical Exam
- Breast Assessment/Examination
- Toxicity/Adverse event evaluation
- Breast Imaging
- Breast Digital Picture (see section 5.1.12 for details)
- Patient and Physician Cosmesis forms

**5.3 Follow-up Procedures**

Subject will be followed at 1 month post-radiation and 3, 6, 12, 24, and 36 months after completion of (or early withdrawal from) study treatment. Time points should follow the visit windows listed under Section 5.4 Time and Events table.

## 5.4 Time and Events Table

|                                                   | Pre-XRT         | Within 14 days after XRT | 1 month after XRT  | Time of surgery | 1 month after surgery  | 3 months after XRT  | 6 months after XRT  | 12 month after XRT  | 24 months after XRT  | 36 months after XRT  |
|---------------------------------------------------|-----------------|--------------------------|--------------------------------|-----------------|------------------------------------|---------------------------------|---------------------------------|---------------------------------|----------------------------------|----------------------------------|
| Procedures                                 |                 |                          |                                |                 |                                    |                                 |                                 |                                 |                                  |                                  |
| Informed Consent                                  | X               |                          |                                |                 |                                    |                                 |                                 |                                 |                                  |                                  |
| History and PE                                    | X               |                          | X                              |                 |                                    |                                 | X                               | X                               | X                                | X                                |
| Breast Assessment/ Examination                    | X               |                          | X                              |                 |                                    |                                 | X                               | X                               | X                                | X                                |
| Performance Status                                | X               |                          |                                |                 |                                    |                                 |                                 |                                 |                                  |                                  |
| Pregnancy Test                                    | X               |                          |                                |                 |                                    |                                 |                                 |                                 |                                  |                                  |
| Baseline AE Evaluation                            | X               |                          |                                |                 |                                    |                                 |                                 |                                 |                                  |                                  |
| Toxicity/AE Evaluations (including DLT)           |                 |                          | X                              |                 |                                    | X                   | X                               | X                               | X                                | X                                |
| Breast Imaging (Mammogram/ US, and or Ultrasound) | X               |                          |                                |                 |                                    |                                 |                                 | X                               | X                                | X                                |
| Breast MRI                                        | X   |                          | X                  |                 |                                    |                                 |                                 |                                 |                                  |                                  |
| Breast Digital Picture                            | X   |                          |                                |                 |                                    |                                 |                                 |                                 |                                  | X                                |
| Patient Cosmesis Forms (Appendix III)             | X  |                          |                                |                 |                                    |                                 |                                 |                                 |                                  | X                                |
| Physician Cosmesis Forms (Appendix IV)            | X  |                          |                                |                 |                                    |                                 |                                 |                                 |                                  | X                                |
| Optional Blood Samples                            | X   |                          | X                              |                 | X                                  |                                 |                                 |                                 |                                  |                                  |
| Tumor Sample                                      | X   |                          |                                | X               |                                    |                                 |                                 |                                 |                                  |                                  |
| Optional Tumor Sample                             | X   | X            |                                |                 |                                    |                                 |                                 |                                 |                                  |                                  |

1 Follow-ups can be done within +/- 21 days of time points above and can be done via telehealth

2 Follow-ups can be done within +/- 60 days of time points above and can be done via telehealth

3 To be completed within 30 days prior to radiation

4 Baseline MRI or contrast enhanced digital mammography(CEDM) is required, Post-radiation MRI is optional but highly recommended and if done, post radiation MRI must be completed at least four weeks after XRT and before surgery.

5 Completed via phone evaluation by study team member

6 Optional tumor sample collection can be done within +2 days of time point above

7 Archival or diagnostic tumor samples

8 Optional tumor sample to be completed within 30 days prior to radiation

9 Should be taken prior to radiation therapy

10 Patient and Physician cosmesis can be completed any time after consent but prior to radiation treatment

## 5.5 Removal of Subjects from Study

Subjects can be taken off the study treatment and/or study at any time at their own request, or they may be withdrawn at the discretion of the investigator for safety, behavioral or administrative reasons. The reason(s) for discontinuation will be documented and may include:

- 5.5.1 Subject voluntarily withdraws from treatment (follow-up permitted);
- 5.5.2 Subject withdraws consent (termination of treatment and follow-up);
- 5.5.3 Subject is unable to comply with protocol requirements;
- 5.5.4 Subject demonstrates disease progression (unless continued treatment with study drug/treatment is deemed appropriate at the discretion of the investigator);
- 5.5.5 Subject experiences toxicity that makes continuation in the protocol unsafe;
- 5.5.6 Treating physician determines continuation on the study would not be in the subject's best interest;
- 5.5.7 Subject becomes pregnant (pregnancy to be reported along same timelines as a serious adverse event);
- 5.5.8 Development of second malignancy (except for basal cell carcinoma or squamous cell carcinoma of the skin) that requires treatment, which would interfere with this study;
- 5.5.9 Lost to follow-up. If a research subject cannot be located to document survival after a period of 2 years, the subject may be considered "lost to follow-up." All attempts to contact the subject during the two years must be documented

## 6.0 MEASUREMENT OF EFFECT

### 6.1 Antitumor Effect - Solid Tumors

#### 6.1.1 Definitions

Evaluable for toxicity. All subjects will be evaluable for toxicity from the time of their first treatment with study therapy.

Evaluable for objective response. Only those subjects who have measurable disease present at baseline, have received radiation, and have had their disease re-evaluated will be considered evaluable for response. These subjects will have their response classified according to the definitions stated below. (Note: Subjects who exhibit objective disease progression prior to the end of cycle 1 will also be considered evaluable.)

#### **Diagnosis of Breast Cancer Recurrence and Other Cancer Events**

Ipsilateral in-breast recurrence: The definition of treatment failure is histologic evidence of recurrent carcinoma, either invasive or non-invasive (except LCIS) in the ipsilateral breast or chest wall. Clinical evidence of carcinoma by physical examination and/or mammograms will not be construed as evidence of treatment failure without biopsy proof but will be considered as suspicious for recurrence. Ipsilateral breast recurrences will be considered local (infield) if they occur within the prescription isodose volume; they will be considered peripheral if they occur between the prescription isodose volume and a volume 2 cm outside of the prescription isodose volume. Ipsilateral recurrences will be considered non-contiguous or extrafield if they are beyond the peripheral volume described above.

Regional recurrence:

Defined as the development of tumor in the ipsilateral mammary, ipsilateral supraclavicular, ipsilateral infraclavicular and/or ipsilateral axillary nodes, as well as the soft tissue of the ipsilateral axilla after operation.

Distant recurrence: Defined as evidence of tumor in any area of the body diagnosed with positive cytology, histologic biopsy, or radiologic evidence of metastatic disease.

Distant Disease-Free Interval: The distant disease-free interval will be measured from the date of registration until the date of first diagnosis of distant disease.

Recurrence free survival: Time from registration to first diagnosis a local, regional, or distant recurrence.

Overall Survival: The survival time will be measured from the date of accession to the date of death. All patients will be followed for survival. Every effort should be made to document the cause of death.

Disease-Specific Survival: will be measured from the date of study entry to the date of death due to breast cancer. The following will be considered as failure events in assessing disease specific survival:

Death certified as due to breast cancer.

Death from other causes with active malignancy.

Death due to complications of treatment, irrespective of the status of malignancy. Death from other causes with previously documented relapse as defined above but inactive at the time of death will not be considered in disease-specific survival, but will be analyzed separately.

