### 2.2 Secondary Objectives

- 2.2.1 Local Control
- 2.2.2 Acute Toxicity (90 Days)
- 2.2.3 Late Toxicity (24 months)
- 2.2.4 Rates of Surgical Morbidity
- 2.2.5 Pathologic Complete Response Rates
- 2.2.6 Patient and Physician Cosmesis Outcomes
- 2.2.7 Distant Disease-Free Survival

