### **6.1.3 Progression-Free Survival**

Progression-free survival (PFS) is defined as the duration of time from start of treatment to time of progression.

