### **10.3 Data Analyses**

#### Data Analysis Plans

Interim Reports: Interim reports will be prepared every twelve months from time of enrollment of first patient until enrollment is complete. In general, the interim reports will contain information about patient accrual rate with projected completion dates of the trial, status of QA review and compliance rate of treatment per protocol, and the frequencies and severity of toxicity.

The dose-limiting toxicity (DLT) and the maximum tolerable dosage (MTD) will be determined based on this Phase I design. The assessment of safety will be mainly based on the frequency of adverse events. The incidence of AEs together with the 95% confidence interval will be reported. The overall complete response rate and corresponding 95% confidence interval will be presented. Various survival rates such as local control, recurrence free survival, and distant disease-free interval will be computed using Kaplan-Meier curves along with the 95% confidence interval. Exact binomial method will be used to calculate the response rate, toxicity and the corresponding 95% confidence interval.

- Kaplan-Meier method will used to estimate the distant disease-free interval.

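### Distant disease-free survival is a stated secondary endpoint but is never defined; the interval analysed in its place, and recurrence-free survival, both leave out deaths

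*Protocol*

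**What the plan says.** - **Objective and endpoint.** Protocol 2.2 lists "Distant Disease-Free Survival" as the seventh secondary objective. The secondary endpoints in 10.1 list it again. Neither place defines it.
- **Definition.** The only distant time-to-event definition is in 6.1.1, under the recurrence and other cancer events heading, and it is of an interval: "The distant disease-free interval will be measured from the date of registration until the date of first diagnosis of distant disease".
- **Recurrence-free survival.** The same section gives "Time from registration to first diagnosis a local, regional, or distant recurrence". Death is not mentioned.
- **Analysis.** Section 10.3 states: "Various survival rates such as local control, recurrence free survival, and distant disease-free interval will be computed using Kaplan-Meier curves". A bullet in 10.3 and the statistical methodology row of the synopsis repeat Kaplan-Meier for the distant disease-free interval. Neither names DDFS.
- **Deaths.** Section 6.1.1 follows every patient for survival and asks for the cause of death. For disease-specific survival it lists which deaths count, including deaths from complications of treatment.
- **Progression-free survival.** Section 6.1.3 says it "is defined as the duration of time from start of treatment to time of progression". It is not an objective, not an endpoint in 10.1, and not named in 10.3.

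**The concern.** A stated endpoint and the quantity planned for estimation are different things. DDFS, by its name, should fall when a patient dies. The interval defined in 6.1.1 does not. If the interval estimate is reported against objective 2.2.7, a reader will take it as the proportion alive and free of distant disease when it is not.

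RFS has the same fault under its own label: it is called survival, is to be estimated by Kaplan-Meier, and has no death event. The omission is hard to read as shorthand, because the same section spells out the qualifying deaths for disease-specific survival.

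Non-cancer death is a realistic event here. Eligibility (3.1) sets a minimum age of 18 and no maximum, and 4.3.1 makes specific provision for women of 70 and over.

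**Working it through.** The protocol states no figure for these endpoints, so there is nothing to reproduce. The check has two parts.

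**1. Definitions side by side**

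| Quantity | Objective or endpoint? | Events in its definition | Named for Kaplan-Meier in 10.3? |
|---|---|---|---|
| DDFS | Yes (2.2.7, 10.1) | None given | No |
| Distant disease-free interval | No | Distant disease | Yes |
| RFS | No | Local, regional or distant recurrence | Yes |
| Progression-free survival | No | Progression | No |

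Kaplan-Meier needs each patient to end in an event or be censored. With death outside the event definition and no other rule stated, a patient who dies without recurrence is censored at death.

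**2. Size of the gap for the distant endpoint**

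Inputs:
- *r*, rate of distant recurrence: assumed 0.5-2% per year.
- *d*, rate of death without distant recurrence: assumed 0.5-3% per year.
- *T* = 3 years, the last scheduled visit (36 months, 4.5 and 5.4). *T* = 5 years is also shown, because 4.5 states five years of follow-up.
- *N* = 60, the maximum in 10.2.

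Assuming constant, independent rates:
- Interval estimate with deaths censored: exp(-rT)
- DDFS with death as an event: exp(-(r+d)T)
- Gap: the first minus the second
- Share dying without distant recurrence: d/(r+d) × (1 - exp(-(r+d)T))

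| T | r | d | Interval estimate | DDFS | Gap (points) |
|---|---|---|---|---|---|
| 3 | 2% | 0.5% | 94.2% | 92.8% | 1.4 |
| 3 | 1% | 1% | 97.0% | 94.2% | 2.9 |
| 3 | 1% | 3% | 97.0% | 88.7% | 8.4 |
| 3 | 0.5% | 3% | 98.5% | 90.0% | 8.5 |
| 5 | 2% | 0.5% | 90.5% | 88.2% | 2.2 |
| 5 | 0.5% | 3% | 97.5% | 83.9% | 13.6 |

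(Gaps are taken before rounding.)

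Over the whole assumed grid the gap runs from 1.4 to 8.5 points at 3 years and from 2.2 to 13.6 at 5 years. It is driven almost entirely by *d* and is close to the share dying without distant recurrence. With r = 0.5% and d = 3%, about 5.13 of 60 patients (5.13/60 = 8.6%) die first by 3 years, against a gap of 8.5 points. Across the grid, 0.9 to 5.1 such deaths are expected among 60 patients by 3 years.

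The same algebra applies to RFS, with *r* read as the rate of any recurrence and *d* as death without any recurrence.

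**3. Is the interval itself biased?**

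As an estimate of distant recurrence alone, one minus Kaplan-Meier can be compared with the cumulative incidence r/(r+d) × (1 - exp(-(r+d)T)). The largest difference on the grid is at T = 5, r = 2%, d = 3%: 1 - exp(-0.10) = 9.52%, against 0.4 × (1 - exp(-0.25)) = 8.85%, or about 0.7 points.

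**The case against.** The best defence has four parts.

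- **An interval that excludes death is a legitimate endpoint.** This stands. The definition in 6.1.1 is not wrong in itself; the fault is that it does not match the objective and endpoint.
- **Censoring of deaths is nowhere written, and a statistical analysis plan could set the rule.** It is indeed an inference from the method and the definitions. But a plan that counted deaths would have to override the protocol's own definition of RFS and supply a DDFS definition that the protocol lacks. The conflict is already in the protocol.
- **The list of Kaplan-Meier endpoints in 10.3 is open-ended, so DDFS may yet be estimated.** This is possible, so it would be too strong to say that DDFS can never be estimated. As written, though, the only distant quantity named is the interval, in 10.3 and in the synopsis.
- **Little depends on it.** This stands. The endpoints are descriptive and the trial has at most 60 patients.

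A reader might also infer more than the documents support:

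- *That progression-free survival will be estimated wrongly.* Its definition omits death, but no planned analysis uses it.
- *That treatment-related deaths vanish.* They count in overall and disease-specific survival, and a grade 5 toxicity definitely attributed to therapy is a dose-limiting toxicity.
- *That the differing time origins (registration, start of treatment) bias the results.* No delay or resulting bias can be shown from the protocol.
- *That recurrence is materially overstated because death competes.* The difference is at most about 0.7 points at 5 years under the assumed rates.
- *That comparison with outside results would mislead.* The protocol sets no DDFS benchmark and plans no such comparison.

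**Conclusion.** The concern holds in a limited form. DDFS is a stated endpoint without a definition, and the planned analysis addresses a different quantity. RFS carries a survival label but counts no deaths. Reported as survival, both would be too high by roughly the proportion who die without the relevant recurrence.

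For the distant endpoint that is about 1.4-8.5 points at 3 years. The range rests on assumed constant, independent rates that the protocol does not supply. If no patient dies without recurrence, the gap is zero.

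Severity is minor: no dose decision, sample size or hypothesis test rests on these estimates.

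**What to change.** Choose one of two routes.

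1. **Keep the survival endpoints.** In 6.1.1, define DDFS as time to distant recurrence or death from any cause, and add death from any cause to RFS. Name DDFS in the Kaplan-Meier sentence of 10.3 and in the synopsis. Keep the distant disease-free interval only under that label, as a separate quantity.
2. **Keep the interval.** Rename objective 2.2.7, the matching endpoint in 10.1, and RFS as intervals, so that no reported figure is called survival while leaving out deaths.

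Under either route, correct the unused progression-free survival definition in 6.1.3 in the same way, or delete it.

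The cost is definition wording. Deaths are already collected for overall survival, so no new data are needed. Under the first route the reported rates may be somewhat lower. Under the second the figures do not change, but the objective becomes narrower.
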